## Abstract

**Background:**

Eighty percent of children with steroid-sensitive nephrotic syndrome (SSNS) relapse within 2 years and 40–50% patients show frequently-relapsing nephrotic syndrome (FRNS). Patients showing a relapse within 6 months after initial remission are at high risk of FRNS. Since frequent prednisolone treatment for FRNS induces severe prednisolone side effects, development of a treatment to prevent patients from shifting to FRNS is desirable. Mizoribine is an immunosuppressive drug with fewer side effects than prednisolone. Recent studies reported the efficacy of high-dose mizoribine in children with FRNS.

**Methods/design:**

We conduct a multicenter, open, randomized controlled trial to investigate the efficacy and safety of standard prednisolone plus high-dose mizoribine therapy in children with SSNS showing a relapse within 6 months after an initial remission. Patients are allocated to either standard prednisolone alone treatment group, or standard prednisolone plus high-dose mizoribine group. For the former group, mizoribine is administered at a dose of 10 mg/kg/day once daily and continued for 2 years. The primary endpoint is the duration to frequent relapse.

**Discussion:**

The results provide important data on use of high-dose mizoribine to prevent SSNS patients from shifting to FRNS. Since blood concentrations of mizoribine have not been investigated in detail until now, there is a possibility that mizoribine is underestimated in favor of other immunosuppressive drugs. In future, high-dose mizoribine therapy may lead to prevention of relapse in children at high risk of FRNS, and to decreased total dose of prednisolone.

**Trial registration:**

UMIN000005103, (Prospectively registered 1st March 2011).

## Background

Prednisolone (PSL) is the first-line drug for the treatment of idiopathic nephrotic syndrome (NS) in children. Ninety percent of patients with childhood NS have steroid-sensitive nephrotic syndrome (SSNS) and remit within 4 weeks after initiation of PSL therapy. After remission, patients require no drug treatment until relapse. Approximately 80% of patients with SSNS relapse within 2 years of PSL treatment as part of the International Study of Kidney Disease in Children (ISKDC) regimen. Around 40 to 50% of patients shift to either “frequently-relapsing NS (FRNS)” as repeating relapse in a relatively short period, or “steroid-dependent NS (SDNS)” as relapsing with decreasing or stopping PSL [1].

Frequent PSL treatment becomes problematic because of the side effects of steroids in FRNS patients. It is clear that patients who relapse immediately (within 6 months) after remission by PSL treatment for the first episode of NS tend to shift to FRNS [2]. It is therefore desirable to inhibit patients from relapsing soon after remission and to avoid the shift to FRNS.

Mizoribine is known to be safer than other immunosuppressive drugs due to its pharmacological characteristics [3, 4]. A placebo-controlled randomized trial in children with FRNS demonstrated that mizoribine has an inhibitory effect for relapsing only in patients 10 years old or younger [3]. Conventional use of mizoribine (3–4 mg/kg daily) leads to a peak blood level at around 1.0 μg/mL [5] although a peak blood level of 2.5–3.0 μg/mL is needed to sustain long-term efficacy for treatment of glomerular diseases [6, 7]. It is thought that children need to take double the dosage of mizoribine as adults because the volume of extracellular fluid of children is larger than in adults and interstitial drug absorption efficacy of children might be lower [8–11].

Recently, high-dose mizoribine administrations aimed to keep high serum mizoribine concentration have been considered for children with FRNS [12, 13]. Serum concentration after 2 h of mizoribine administration (C2) was about 3 μg/mL in patients who achieved decrease in the number of relapses. These patients took 10 mg/kg/day of mizoribine once a day, and there were no severe side effects.

Patients with NS under 10 years old and who relapse within 6 months after remission for the first episode of NS are considered to be high risk of FRSN [2]. We therefore focus on the possibility that adding high-dose mizoribine to the standard PSL treatment for SSNS patients who are likely to shift to FRNS could prevent them from shifting to FRNS. Here, we conduct a multicenter open randomized controlled trial to evaluate the efficacy and safety of PSL plus high-dose mizoribine treatment.

## Methods/design

### Aim

This trial aims to investigate whether standard PSL plus high-dose mizoribine combination therapy is superior to standard PSL alone in preventing a shift to FRNS for children with SSNS who immediately (within 6 months) relapse after remission with the ISKDC PSL treatment for the first episode of NS.

### Study design and patients

We conduct a multicenter, randomized, superiority, open-label trial and compare standard PSL plus high-dose mizoribine combination treatment with standard PSL alone treatment for children with SSNS who immediately (within 6 months) relapse after remission for the first episode of NS (Fig. 1). We diagnose NS and remission according to the ISKDC. Patients aged 2–10 years are eligible if they have remission within 3 weeks of PSL administration for the first relapse.

**Fig. 1 Fig1:**
[figure not shown]
Treatment regimens

Inclusion and exclusion criteria are as follows:Inclusion criteria:Patients diagnosed with a first episode of NS who meet (a) urinary protein/creatinine ratio ≥ 1.8 and (b) ≤2.5 g/dL of serum albuminPatients treated by the ISKDC based regimen at the first episode and relapsed within 6 months after the first remissionAge at the registration ≥2 and < 11 yearsPatients who remit within 3 weeks after PSL treatment for the first relapseExclusion criteria:Patients diagnosed with nephritic NSPatients diagnosed with IgA vasculitis, systemic lupus nephritis or secondary NSPatients who have been diagnosed with steroid-resistant NS (SRNS)Patients who have been treated with any immunosuppressant for NSPatients with poorly controlled hypertension, impaired renal function, or severe liver dysfunctionPatients who are participating in other studies at the time of registration.

### Randomization

Patients are randomly assigned to either the standard PSL plus high-dose mizoribine combination, or standard PSL alone group in a 1:1 ratio. We use a minimization method stratifying by age (2–5 years or 6–10 years), sex, duration from initial remission to relapse (< 90 days or ≥ 90 days) and institution as adjustment (stratification) factors. Patients, their guardians, treating physicians, and individuals assessing outcomes and analyzing data are not blinded to the patients’ treatment assignments. Apart from the trial statistician and the data-monitoring committee, all treating physicians and other investigators remain blinded to the trial results until follow-ups are completed.

### Procedures

For the standard PSL plus high-dose mizoribine group, mizoribine is administered at a dose of 10 mg/kg/day (maximum 300 mg/day) once daily after breakfast and continued for 2 years. Mizoribin is started within 7 days from the registration date. After 2-year administration or termination of this trial, dosage of mizoribine will be tapered every month and stopped within 3 months. In case of leukocytopenia or impaired renal function, mizoribine treatment will be tapered or stopped. PSL treatment for relapse during the observation period follows the ISKDC regimen.

The observation period is from the registration date to the completion or discontinuation date of this trial. Completion of study is defined as completing of 2-year administration. Patients who complete or discontinue this study will be followed-up.

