### Outcomes

The primary endpoint is defined as the duration from registration to diagnosis of FRNS. Diagnosis of FRNS is based on relapse dates according to the ISKDC. In our study, FRNS is defined as two relapses within 6 months of initial remission, or four relapses within any 12-month period. This includes relapses during initial tapering treatment, but excludes relapses with spontaneous remissions. Relapse is defined as proteinuria 2+ or higher on dipstick analysis for 3 or more consecutive days or proteinuria 2+ or higher on dipstick analysis and serum albumin ≤2.5 g/dL. Immunosuppressant administration is prohibited in the protocol. If patients show SDNS or SRNS, they are treated as an event in the primary analysis. Data for patients who do not experience these events are considered censored at the last examination. Secondary endpoints are relapse-free period, the poportion of patients without relapses, the number of relapses per person/year, time to SDNS, time to SRNS, total prednisolone dose, and adverse events. Adverse events were recorded throughout the trial period and assessed using Common Terminology Criteria for Adverse Events v3.0. Serum mizoribine concentrations at trough and C3 are measured 1 month after administration of mizoribine to monitor safety and pharmacological effect.

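### The end of observation is tied to completing 2 years of administration, which only the mizoribine arm has, and it is unclear whether later events count for the primary endpoint

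*Protocol article*

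**What the plan says.** Procedures in the Protocol article sets the window: "The observation period is from the registration date to the completion or discontinuation date of this trial". The next sentence fixes one of its two ends: "Completion of study is defined as completing of 2-year administration". It then adds: "Patients who complete or discontinue this study will be followed-up". How long that follow-up lasts, and whether it feeds the primary analysis, is not stated.

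The only treatment described as lasting 2 years is mizoribine, and it belongs to one arm: "For the standard PSL plus high-dose mizoribine group, mizoribine is administered at a dose of 10 mg/kg/day (maximum 300 mg/day) once daily after breakfast". Early stopping is foreseen: "In case of leukocytopenia or impaired renal function, mizoribine treatment will be tapered or stopped". Prednisolone is given for relapses and has no 2-year course.

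Outcomes gives the censoring rule for the primary endpoint: "Data for patients who do not experience these events are considered censored at the last examination". Two further conditions count as events: "If patients show SDNS or SRNS, they are treated as an event in the primary analysis". The same section states: "Immunosuppressant administration is prohibited in the protocol". It does not say how a child who starts one before reaching the endpoint is handled. Randomization says that families, physicians and outcome assessors all know the allocation.

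**The concern.** The end of the window for the primary endpoint depends on something that happens after randomisation and exists in one arm only. A child who stops mizoribine early can no longer complete as defined, and the only other end that Procedures names is discontinuation. A child on prednisolone alone has no administration to complete.

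The log-rank test and the Cox model assume that censoring is unrelated to prognosis within each arm. Frequent relapse is reached by accumulating relapses, so a child may leave after one or two of them, when risk is visibly high but the endpoint has not been met. In an open trial, families and physicians may act on that differently in the two arms. If such children are censored when they leave, the hazard ratio no longer compares the randomised groups cleanly. Two competent analysts could also build different primary datasets from the present text.

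**Working it through.** **1. The sections side by side**

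| Child | End of observation, Procedures read literally | Censoring date, Outcomes |
|---|---|---|
| Mizoribine, 2 years taken | Completion | Last examination |
| Mizoribine, stopped early, still attending visits | Cannot complete; not said to have discontinued the trial | Last examination, in the window or in later follow-up: not stated |
| Prednisolone alone, still attending visits | No completion defined | Last examination |
| Either arm, left the trial, later followed up | Discontinuation; follow-up comes after the window | Not stated whether follow-up examinations count |

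Only the first row has a clear end.

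**2. The plan's own sample size**

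Inputs from Statistical analyses: 50% with the endpoint at 2 years in control, hazard ratio (HR) 0.50, two-sided 5%, 80% power, 4 years of accrual and 2 years of follow-up. Exponential times are assumed.

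- Events (Schoenfeld): 4(1.960 + 0.842)² / (ln 0.5)² = 65.4, so 66.
- Hazards: ln 2 / 2 = 0.3466 per year in control and 0.1733 with mizoribine.
- Uniform accrual over 4 years and a common calendar end 2 years later, so 2 to 6 years per child: P(event) = 1 − (e^(−2λ) − e^(−6λ)) / (4λ). This gives 0.7295 and 0.4899, mean 0.6097.
- N = 66 / 0.6097 = 108.2 (Lakatos method 108.5). The stated 108 is reproduced, and 108 / 0.90 = 120.

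If each child is instead observed for 2 years only, as the definition of completion suggests:

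- P(event) = 0.500 and 1 − √0.5 = 0.293, mean 0.3965.
- Expected events are 108 × 0.3965 = 42.8 and 120 × 0.3965 = 47.6.
- Power = Φ(√d × 0.693 / 2 − 1.96), which is Φ(0.308) = 62% at 108 and Φ(0.430) = 67% at 120.
- N needed = 66 / 0.3965 = 166.5, so 167 (Lakatos 171), before any withdrawal allowance.

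**3. What censoring at discontinuation could do**

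The document gives no discontinuation rate, so everything here is assumed. Simulation: 60 per arm, 2 years each, 8,000 trials per cell. In both arms a fraction of children carry 1, 2 or 3 times the risk of the rest, with the average risk held fixed. In the mizoribine arm only, those children are censored at a uniform time in year 1. The true HR is 1.0. Cells show the mean estimated HR and the rate of false rejection in favour of mizoribine (nominal 2.5%).

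| Share stopping | Same risk | 2 times | 3 times |
|---|---|---|---|
| 5% | 0.992 (2.7%) | 0.975 (3.2%) | 0.969 (3.3%) |
| 10% | 0.998 (2.7%) | 0.957 (3.2%) | 0.933 (4.6%) |
| 20% | 0.994 (2.4%) | 0.915 (4.7%) | 0.863 (7.4%) |

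With the same children kept under observation, the HR is 0.998 to 1.004 and false rejection 2.3% to 2.7%. With a true HR of 0.50, censoring stoppers at 2 to 3 times the risk gives about 0.48, 0.46–0.47 and 0.43–0.45 at 5%, 10% and 20% stopping.

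A different mechanism gives similar sizes. Here exit follows a non-qualifying relapse, in the mizoribine arm only, with no true effect and 1,200 trials per setting. The HR is 0.94 when 13% of the arm leaves and 0.88 when 24% leaves, with false rejection of 4.3% and 6.3%. That model used the relapse-count rule alone and did not count steroid dependence or resistance as events.

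**4. The opposite direction**

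Under no effect the arms are interchangeable, so the same exits from control alone mirror the result: 1 / 0.863 = 1.16 in place of 0.86, and 1 / 0.969 = 1.03 in place of 0.97. Equal exits in both arms leave the expected log HR at 0.

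**The case against.** A reader might infer that stopping mizoribine ends participation and so produces one-sided censoring in favour of mizoribine. The document does not say this. Procedures speaks of tapering or stopping the drug in one sentence and of discontinuing the trial in another, and never equates them. Outcomes censors at the last examination and does not mention the observation period. Follow-up after discontinuation is promised. The sample size also points away from a hard stop, because it counts events beyond 2 years. No sentence describes an on-treatment analysis.

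Nor is the direction given. Control children can also leave, and the immunosuppressant prohibition is not confined to one arm. Exits by relapsing control children would bias against mizoribine. The simulations place all exits in one arm by assumption. The plan's only figure is the 10% allowance for withdrawal and loss, across both arms.

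Finally, analysis populations and detailed censoring rules are commonly left to the full protocol or analysis plan, which are not shown.

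All of this stands against the stronger reading. It does not remove the point, because the fault lies in rules the article does state. Completion is defined by a milestone that does not exist for one arm. The follow-up sentence applies after the window has closed. The last examination can be read either way.

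**Conclusion.** The definition is faulty and should be corrected. The end of observation is not defined alike in the two arms, and it is unclear whether events after discontinuation count for the primary endpoint. If they do not, censoring can be differential and informative.

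The document does not establish that such bias will occur, that it is one-sided, or that it favours mizoribine. If stopping is unrelated to risk there is no material bias (HR 0.99 to 1.00). If 5% to 20% of the mizoribine arm stop at three times the risk of the others and nobody leaves control, an HR of 1.0 is estimated at 0.97 down to 0.86. These figures rest on assumed rates, exponential times and 2 years of observation, and they show only what could be at stake.

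One consequence is firm under the plan's own inputs. A 2-year window per child and a sample size of 108 at 80% power cannot both hold.

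**What to change.** - Define one end of observation, counted from registration or set as a calendar date, the same in both arms and independent of whether mizoribine is continued.
- State that stopping mizoribine or other protocol treatment does not end observation.
- Count frequent relapse, steroid dependence and steroid resistance found in the follow-up already planned, in the arm to which the child was allocated.
- Censor only at withdrawal of consent, loss to follow-up or the common end.

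Choose that end together with Statistical analyses. A calendar end 2 years after the last registration agrees with 108 at 80% power, but it also counts events after the planned 2 years of mizoribine and relies on the HR staying at 0.50 over that time. A limit of 24 months per child avoids this, but power must then be restated as about 62% at 108 or 67% at 120, or the target raised to 167–171 before the withdrawal allowance. Procedures and Statistical analyses must be reconciled either way.

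The cost is mainly wording, plus making sure that relapse dates are recorded in the same way after discontinuation. The HR becomes a treatment-policy effect, somewhat diluted by stopping. Nothing about dose or clinical care changes.

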Historically, mizoribine has been used to suppress rejection reactions in kidney transplantation [20, 21], lupus nephritis [22, 23] and rheumatoid arthritis. Mizoribine has also been reported to be effective as a treatment for IgA nephropathy [24, 25]. It is approved as a treatment of NS in Japan [3, 26]. By adding mizoribine, the total dose of steroids can reportedly be reduced in treatment for NS. [27]. Furthermore, a double-blind, placebo-controlled, multicenter trial has shown that mizoribine significantly decreased relapse rate and prolonged remission period in children with FRNS in the subgroup consisting of patients 10 years old or younger [3]. Although efficacy and safety of mizoribine are well recognized in medical practice, blood concentration of mizoribine has not always been sufficient to reach efficacy. There is therefore a possibility that mizoribine is underestimated compared to other immunosuppressive drugs. Conventional use of mizoribine (3–4 mg/kg daily, maximum 150 mg/day) leads to a peak blood level at around 1.0 μg/mL [5], although a peak blood level of 2.5–3.0 μg/mL is biologically required to sustain long-term efficacy for the treatment of glomerular diseases [6, 7]. Consequently, high-dose mizoribine administrations aiming to retain high serum mizoribine concentration have come to be considered for children with FRNS [12, 13]. Serum C2 concentrations are known to be around 3 μg/mL in patients who achieved decrease in the number of relapses by taking 10 mg/kg/day of mizoribine once a day without severe side effects. Therefore, in the current protocol, we adopted dosage of 10 mg/kg/day of mizoribine once a day (maximum 300 mg/day).

If we can prevent at-risk patients from shifting to FRNS by adding high-dose mizoribine effectively and safely, we will reduce the total dose of steroids for patients, resulting in less side effects. Moreover, we will avoid use of other immunosuppressants, such as cyclosporine and cyclophosphamide, which are proven to be more effective but have more serious side effects than mizoribine. Patients with mizoribine treatment do not require frequent blood tests or renal biopsy, which is seen as a great benefit. As a result, it is expected to reduce medical expenses despite cost of mizoribine.

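### As the Procedures section reads, efficacy is observed only until mizoribine ends, so a positive result would not show that the effect lasts; the article's sections also disagree on the analysis horizon

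*Protocol article*

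**What the plan says.** The Aim section of the protocol article asks whether the combination "is superior to standard PSL alone in preventing a shift to FRNS". Under Procedures, mizoribine is given "once daily after breakfast and continued for 2 years". The same section sets the window: "The observation period is from the registration date to the completion or discontinuation date of this trial", and "Completion of study is defined as completing of 2-year administration". It puts withdrawal of the drug later: "After 2-year administration or termination of this trial, dosage of mizoribine will be tapered every month and stopped within 3 months". It then adds: "Patients who complete or discontinue this study will be followed-up". No length, schedule or purpose is given for that follow-up.

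The Outcomes section defines the primary endpoint as time from registration to an FRNS diagnosis, with steroid-dependent and steroid-resistant disease (SDNS, SRNS) also counted as events. A child without an event is censored at whichever examination came last, and no 2-year limit is stated. None of the secondary endpoints refers to time after the study or off the drug.

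The Statistical analyses section bases the 108 patients on a control probability of 50% at 2 years, a hazard ratio of 0.50, two-sided 5% alpha, 80% power, 4 years of accrual and 2 years of follow-up.

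**The concern.** For a child who completes, the Procedures section closes observation before the drug is reduced. A child held in remission on mizoribine at month 24 who relapses repeatedly after the taper would count as free of FRNS. A 2-year reading gives the same answer whether the drug changes the course of the disease or holds relapses down only while it is taken.

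The difference matters for what is concluded. The Discussion expects, on condition that the shift is prevented, a lower total steroid dose and more: "Moreover, we will avoid use of other immunosuppressants, such as cyclosporine and cyclophosphamide". For the years after treatment, that expectation depends on what happens once mizoribine stops, and no stated endpoint looks there.

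The horizon is also not settled. The Outcomes section and the sample size point to observation well beyond 2 years. If that is the plan, off-drug time enters the primary hazard ratio without being separated from on-drug time.

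**Working it through.** **Inputs (Statistical analyses section).** Control FRNS probability 50% at 2 years; hazard ratio 0.50; two-sided alpha 5%; power 80%; accrual 4 years; follow-up 2 years; 108 patients, raised to 120. Exponential survival is assumed throughout.

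**Hazards.** Control: ln 2 / 2 = 0.3466 per year. Mizoribine: 0.50 × 0.3466 = 0.1733 per year.

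**Step 1: reproduce the 108.** Schoenfeld events: 4 × (1.960 + 0.842)² / (ln 0.5)² = 65.3. With uniform accrual over 4 years and a further 2 years, each child is followed for 2 to 6 years. The event probability is then 1 − [exp(−2h) − exp(−6h)] / (4h).

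- Control: 1 − (0.500 − 0.125) / 1.386 = 0.729
- Mizoribine: 1 − (0.707 − 0.354) / 0.693 = 0.490
- Mean 0.610; 65.3 / 0.610 = 107.2, or 108 with equal arms

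The stated figure is reproduced (a Lakatos-type log-rank calculation gives 110).

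**Step 2: the same inputs read at exactly 2 years, as Procedures defines completion.** Event probabilities are 0.500 and 1 − exp(−0.3466) = 0.293, mean 0.396. 65.3 / 0.396 = 165.

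| Horizon per child | Mean event probability | N for 80% power | Power at 108 | Power at 120 |
|---|---|---|---|---|
| 2 to 6 years | 0.610 | 108 | 80% | 84% |
| Fixed 2 years | 0.396 | 165 | 62% | 67% |

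**Step 3: off-drug events in the longer horizon.** Share of events after year 2:

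- Control: (0.729 − 0.500) / 0.729 = 31%
- Mizoribine: (0.490 − 0.293) / 0.490 = 40%

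By then mizoribine should be in taper or stopped, so the sample size carries a hazard ratio of 0.50 into off-drug time. If the hazard instead returned to control after year 2 (an assumption), a Lakatos-type calculation gives the 2-to-6-year log-rank test about 40% power at 108 and 44% at 120. With a lasting ratio of 0.50 the same method gives 80% at 108.

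**Step 4: what a 2-year reading cannot separate.**

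- At 2 years: 50.0% against 29.3%, a gap of 20.7 points, whatever happens later.
- At 3 years, control: 1 − exp(−3 × 0.3466) = 64.6%.
- At 3 years, mizoribine, lasting ratio of 0.50: 1 − exp(−3 × 0.1733) = 40.5%, a gap of 24.1 points.
- At 3 years, mizoribine, hazard back at control after month 24: 1 − 0.7071 × exp(−0.3466) = 50.0%, a gap of 14.6 points.

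The last line assumes no carry-over and simple reversion.

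**The case against.** A reader might infer that every efficacy endpoint is read on drug and that the trial cannot tell prevention from suppression. The document does not support that. The Outcomes section sets no 2-year cut. The Randomization section keeps investigators from seeing results until follow-up has finished. The sample size needs events up to 6 years after registration. Nothing excludes a follow-up visit from counting as the last examination. Some time inside the observation period may also be off drug, because mizoribine can be stopped for leukocytopenia or impaired renal function. All of this stands. It is why the point is tied to the Procedures definitions and why the sections must be reconciled.

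A reader might also infer that the benefit would vanish within a year. That needs a rebound to twice the control hazard, which would bring both arms to 64.6% at 3 years. Nothing in the document suggests such a rebound. Under simple reversion a 14.6-point gap remains.

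Fewer FRNS diagnoses and less prednisolone over 2 years are worthwhile in themselves, the comparison with prednisolone alone is a legitimate superiority question, and the article nowhere claims an effect after withdrawal. This also stands: the comparison is valid, and only the conclusion needs limiting.

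Finally, an article condenses a fuller protocol, which may define the follow-up and its analysis. The lack of detail is therefore not the finding. The finding is that the window, the censoring rule and the sample-size assumptions stated here do not agree with each other or, on the 2-year reading, with the breadth of the aim.

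**Conclusion.** The point holds in limited form. Under the Procedures definitions, a completer's efficacy observation ends before the taper and no named endpoint uses the promised follow-up. A positive result would then show a reduction in FRNS during 2 years of treatment and would not show whether it outlasts the drug. Simple reversion would shrink the gap from 20.7 points at 2 years to 14.6 at 3 years; larger rebounds are pure assumption.

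If the horizon is instead the 2 to 6 years that the sample size implies, off-drug time is included. A single hazard ratio then pools it with on-drug time and still does not isolate persistence. On neither reading does a stated analysis address the off-drug period by itself. The figures rest on constant hazards and on the plan's 50% and 0.50. The full protocol could settle the horizon.

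**What to change.** 1. State one analysis horizon for the primary endpoint and make the Procedures, Outcomes and Statistical analyses sections agree with it and with the sample size. Define it as time from registration, so that it applies equally to the arm without mizoribine.
2. If the horizon is 2 years, word the aim and conclusion as a reduction in FRNS during treatment, and restate the power (62% at 108, 67% at 120).
3. Add one secondary analysis, as randomised, of time from registration to FRNS, SDNS or SRNS, up to a fixed time point for both arms beyond the end of the taper, using the planned follow-up. Month 39 would be one choice: 24 + 3 + 12 months. Show on-drug and off-drug periods separately. Report later immunosuppressant use by arm, because the article does not say whether the ban on such drugs continues after the study, and unequal use would affect the off-drug comparison.

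Cost: relapse dates and later treatments recorded at follow-up, and one more analysis. The article gives no duration for that follow-up, so fixing one may be new work. With month 39, the last children enrolled would report about 15 months after month 24. A 2-year primary analysis would not be delayed, and treatment is unchanged. The headline claim becomes narrower unless persistence is shown.
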